### Treatment characteristics

*Current and previous treatments* for psychological problems, including complementary and self-help treatments, will be administered with the inventory of History of Treatments (VEHI; [74]). This questionnaire consists of 6 items.

*Treatment integrity* will be established by rating two randomly chosen sessions that are video or audiotaped. Ratings will be done by two independent researchers and interrater reliability will be established.

In the context of this study, other treatment characteristics will not be further described.

### Incentives

To motivate participation in the assessments, we offer adolescents and parents incentives of respectively 35 and 10 euros in total, regardless of study condition. Adolescents will receive 5 euros per assessment and 5 euros bonus after completing all six assessments. Parents will receive 10 euros after completing all three assessments.

### Data analysis

All analyses will be conducted according to the intention-to-treat principle (i.e., all participants, as randomised). Clustering of data will be taken into account, considering that small treatment groups of students (from the same school) will be randomized as a cluster to one of the four conditions. For all analyses multilevel mixed modelling in Stata [75] and Mplus [76] will be used. The four conditions will be included as fixed effects (i.e., by using dummy variables). For treatments groups random effects will be included [77]. Finally, the schools will be included by using fixed rather than random effects, because the between-school variability cannot be estimated well with the small number of available schools (we have included 11 schools so far). Possible baseline differences between the four conditions in depressive symptoms and demographic variables will be analysed. Variables that show differences between the four conditions will be entered as covariates in all models. When the data collection is complete, all members of the research team ([name]) will have access to the full dataset.

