### Recruitment, screening and randomization

Adolescents will be recruited via secondary schools in The Netherlands. All adolescents and their parents (for subjects aged younger than 16) receive written information about the screening and the study. After receiving passive consent, adolescents will be screened with the CDI-2 [50, 52] for depressive symptoms in order to select high-risk adolescents. Students with an elevated level of depressive symptoms will be approached by email and by phone to participate in the study. Written informed consent from adolescents and parents (for subjects aged younger than 16) will be obtained by the first author ([name]) by post or email prior to the initiation of the study. Screening will continue until the planned sample size is achieved (*n* = 256, see subheading ‘sample size’).

Eligible and consenting students from the same school will be stratified by gender (boy or girl) and age (12–13 years, 14–15 years, 16 years or older), because a meta-analytic review found that CBT depression prevention programs showed higher effect sizes for samples with a higher rate of female participants and samples with older participants (> 13.5 years) [53]. Then treatment groups of on average five students (from the same school) will be formed, which are the unit of randomization. The treatment groups will be randomized as a cluster by the first author ([name]), to one of the four conditions, by computer generated block randomization (with a block size of four). Once randomized such a group of students continues as a group receiving the preventive program, with one therapist per group. Blinding of participants is not possible, like in most psychological interventions. However, allocation to the four conditions will be concealed until the introductory meeting, which takes place after the baseline assessment has been completed. The overall study design is shown in Fig. 1**.**

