### Sample size

The trial is well powered with *n* = 64 in each of the four conditions (*n* = 256 in total) to detect a clinically relevant effect (mean standardized difference, *d*) of *d* ≥ 0.33 as statistically significant (at α ≤ 0.05, 2-tailed) with a power of (1-β) ≥ 0.80 when the primary outcome (depressive symptoms) is evaluated in a baseline adjusted analysis of variance (ANCOVA) while also taking into account the nesting in the data owing to the cluster randomized trial.

More specifically, the power calculation was conducted using Stata’s 14.2 sample size procedure (*sampsi*) assuming that the evaluation would be carried out in a baseline adjusted ANCOVA with one baseline assessment and one follow-up (*t*_*1*_). The correlation (*r*) between *t*_*0*_ and *t*_*1*_ (*r* = .80) was estimated from preliminary data. This indicated that 52 respondents per condition were required. In a next step, we calculated the design effect of 1.22 while taking into account the intraclass correlation coefficient (*icc*), the mean cluster size (*m*), the coefficient of variation (*cv*) of the cluster sizes. The *icc* was estimated at 0.05, *m* and *cv* where estimated from preliminary data at 5 and 0.30, respectively. Hence, 64 (52*1.22) participants per condition are needed or a total *n* of 256. We will not increase the sample size at baseline to compensate for dropout, because all analyses will carried out in agreement with the intention-to-treat principle.

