### The program

The prevention program is designed for indicated prevention and will be offered in groups of about five adolescents. The program is developed by the researchers themselves, in close collaboration with CBT-therapists and experts in the field. For each of the four most commonly used CBT-components a module of three sessions is developed; one module with three sessions of cognitive restructuring (CR), one module with three sessions of behavioural activation (BA), one module with three sessions of problem solving (PS) and one module with three sessions of relaxation (RE). The modules were developed based on cognitive and behavioural theories, a taxonomy that describes the techniques that diverse CBT-components should comprise [22], current Dutch CBT-protocols (e.g., The D(o) epression course, [41]; Op Volle Kracht, [43]) and the MATCH-ADTC [46]. In each step of this developing process, a group of certified CBT-therapists and experts in the field was consulted. Also [name] was consulted during the process (December 2016).

The program consists of twelve sessions (4 components * 3 sessions) of 45–60 min each. Prior to the program an introductory meeting will take place which lasts 30 min. The program takes place at the participating schools directly after school, one to two times a week (depending on holidays and schools’ preferences). It will be provided by certified alumni pedagogics/psychology, who are trained in two-and a half days and supervised by psychologists. Treatment adherence of participants will be monitored by the therapists and stimulated if necessary.

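### Each treatment group has one therapist, but the stated model has no therapist term and no stated safeguard keeps therapist assignment independent of condition

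*Protocol article*

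**What the plan says.** Under Recruitment, screening and randomization, treatment groups averaging five students from one school are the unit of randomisation. They are allocated to the four conditions in blocks of four. Each group then continues as a unit, "receiving the preventive program, with one therapist per group". Of the therapists, The program section says: "It will be provided by certified alumni pedagogics/psychology, who are trained in two-and a half days and supervised by psychologists". The article does not give their number, how many groups each leads, whether a therapist works in more than one condition or school, or when a therapist is attached to a group.

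Data analysis sets one model structure for all analyses: condition as fixed dummies, school as fixed effects (with a reason given), and one random level, "For treatments groups random effects will be included". Therapist does not appear. The Sample size section also covers the group level only: "we calculated the design effect of 1.22 while taking into account the intraclass correlation coefficient", together with mean cluster size and the variation in cluster size.

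Therapists do appear among the measures. Table 2 lists therapist demographics and therapist-reported alliance and cooperation.

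**The concern.** With about 51 groups, a therapist may well lead more than one. Therapist would then be a source of correlation above the group, and the group random effect would treat one therapist's groups as independent. The Data analysis section goes as far as arguing for school as fixed rather than random, so the clustering structure is specified and this level is left out of it.

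The stakes are direct because the trial has no untreated control arm, as its limitations section says. Each main result is a difference between active conditions delivered by people, so therapist skill is a rival explanation for any such difference unless therapists are kept independent of condition. The article states nothing that secures this. The blocks of four balance the number of groups per condition, but they are not described as balancing therapists.

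**Working it through.** **Inputs from the Sample size section.** d = 0.33, two-sided α = 0.05, power 0.80; baseline-to-t1 correlation 0.80; ICC "was estimated at 0.05"; mean cluster size m and its cv "where estimated from preliminary data at 5 and 0.30, respectively".

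**Assumed, because the article does not give them.** Groups per therapist g, from 1 to 4. Correlation between students in different groups of the same therapist, ρ_T, from 0.01 to 0.05, taken as part of the stated ICC of 0.05. The upper end puts the whole ICC on the therapist and leaves nothing for the group itself.

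**1. The plan's own figures.**
- n per condition before clustering = 2(1 − 0.80²)((1.96 + 0.842)/0.33)² = 51.9, so 52.
- Design effect = 1 + ((1 + 0.30²) × 5 − 1) × 0.05 = 1.2225.
- 52 × 1.22 = 63.4, so 64 per condition and 256 in total.
- Power at 64 per condition with this design effect = 0.803.
- Number of groups = 256/5 = 51.2, or 12.8 per condition.

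All stated figures reproduce.

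**2. Therapists nested within one condition (formula).** True design effect = 1.2225 + (g − 1) × 5 × ρ_T. The planned analysis still works as if it were 1.2225, so the actual two-sided error is 2(1 − Φ(1.96 × √(1.2225/true design effect))). The power column is for a correct analysis at 64 per condition.

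| g | ρ_T | Design effect | Type I error | Power at 64 per condition |
|---|---|---|---|---|
| 1 | any | 1.22 | 0.050 | 0.80 |
| 2 | 0.01 | 1.27 | 0.055 | 0.79 |
| 2 | 0.02 | 1.32 | 0.060 | 0.77 |
| 2 | 0.05 | 1.47 | 0.074 | 0.73 |
| 4 | 0.01 | 1.37 | 0.064 | 0.76 |
| 4 | 0.02 | 1.52 | 0.079 | 0.71 |
| 4 | 0.05 | 1.97 | 0.123 | 0.60 |

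Example, g = 4 and ρ_T = 0.05: 1.2225 + 3 × 5 × 0.05 = 1.9725; √(1.2225/1.9725) = 0.787; 1.96 × 0.787 = 1.54; two-sided tail 0.123.

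**3. Therapists balanced over conditions (formula).** Therapist variance cancels from the contrast but stays in the estimated error. With equal groups of five and without school effects, the error variance is overstated by (1 + 4 × 0.05)/(1 + 4 × 0.05 − 5ρ_T). At ρ_T = 0.05 this is 1.20/0.95 = 1.26, or 12% on the standard error. At ρ_T = 0.02 it is 1.20/1.10 = 1.09, or 4%.

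**4. Simulation with the planned school fixed effects.** No true effect; 48 groups of five; 11 schools as fixed effects; therapist omitted; analysis of group means, which for equal group sizes matches the planned group random-intercept model; 4,000 runs per setting. Four groups per therapist, except in the one-group and one-per-school rows. Each cell gives ρ_T = 0.02 / 0.05.

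| How therapists are assigned | Pairwise type I error | 3-df test | Model SE against true SE |
|---|---|---|---|
| One group per therapist | 0.052 / 0.045 | 0.056 / 0.048 | correct |
| Nested within condition | 0.085 / 0.118 | 0.099 / 0.170 | 12% / 21% too small |
| Independent of condition | 0.052 / 0.051 | 0.050 / 0.051 | correct |
| One therapist per school | 0.053 / 0.049 | 0.051 / 0.052 | correct |
| Balanced over conditions | 0.042 / 0.032 | 0.038 / 0.023 | 4% / 9% too large |

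Monte Carlo error near 0.05 is about √(0.05 × 0.95/4000) = 0.003.

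**The case against.** Two stronger readings are tempting, and the document supports neither.

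The first is that omitting therapist makes the standard errors of every comparison wrong as soon as therapists lead several groups. The simulation contradicts this. With assignment independent of condition, or one therapist per school (absorbed by the planned school fixed effects), the error stays at about 5%. With one group per therapist, the group random effect already carries the therapist. With balance over conditions, the tests are conservative. Only assignment that follows condition produces false positives.

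The second is that therapists are chosen after the draw. The sentence that mentions them describes how a randomised group receives the program. It does not say when the therapist is assigned, and word order is no evidence of timing.

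It is also fair to say that nothing in the article points to nesting within condition. All conditions deliver the same four modules in different orders, a single training is described, and no condition-specific therapists are mentioned. The number of therapists and the assignment procedure are the kind of operational detail that a condensed article may leave to the full protocol. Putting the entire ICC of 0.05 on the therapist is a worst case.

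These arguments limit the size and certainty of the problem but do not remove it. The harmless layouts are possible, but the article secures none of them, and the model it fixes for all analyses would not detect or correct the harmful one.

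**Conclusion.** The point holds in conditional form. The stated model omits a likely level of clustering, and the article states no safeguard that keeps therapists independent of condition. If therapists lead several groups mostly within one condition, therapist is confounded with condition and standard errors are too small. With four groups each and ρ_T of 0.02 to 0.05, pairwise type I error is about 8 to 12%. A correct analysis would then have power of 0.71 to 0.60 instead of 0.80. If therapists are balanced over conditions, the cost is standard errors about 4 to 9% too large and some lost power. In the remaining layouts examined, the planned analysis is sound.

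These sizes rest on assumed values of g and ρ_T. The article gives neither, so they show what could happen and do not estimate what will.

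**What to change.** - **Design, for groups still to be randomised.** Eleven schools had been included when the article was written and recruitment appears to be continuing, so this can still help. Name the therapist for each group before its condition is drawn and, where feasible, have each therapist lead groups in more than one condition.
- **Analysis.** If any therapist leads more than one group, add a therapist random intercept to the models in Data analysis. If it is weakly identified beside the group random effect and the school fixed effects, report it as a sensitivity analysis.
- **Reporting.** State the number of therapists and how and when they were assigned, and tabulate therapists by condition.

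The cost is a small scheduling constraint and one variance component that may be poorly estimated, especially if most therapists lead only one or two groups. The random intercept corrects the standard errors, but it does not remove confounding for groups already allocated. For those, the table of therapists by condition shows how far the problem reaches.

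### The sample size assumes a baseline-adjusted ANCOVA, but the analysis section enters baseline depressive symptoms only if the arms show differences, by a criterion it does not state

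*Protocol article*

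**What the plan says.** Sample size (protocol article): the trial is said to detect d "≥ 0.33 as statistically significant" with power "≥ 0.80 when the primary outcome (depressive symptoms) is evaluated in a baseline adjusted analysis of variance (ANCOVA"), while also allowing for clustering. The calculation is described as "assuming that the evaluation would be carried out in a baseline adjusted ANCOVA with one baseline assessment and one follow-up", t1, with a correlation of .80 taken from preliminary data.

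Data analysis: the models are multilevel, with condition dummies, random effects for treatment groups and fixed effects for schools. Covariates are then dealt with in two sentences. The first is "Possible baseline differences between the four conditions in depressive symptoms and demographic variables will be analysed". The second is "Variables that show differences between the four conditions will be entered as covariates in all models". No test, significance level or size of difference is given.

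The sections on the main effect of the components and of the sequences name depressive symptoms at t1, t4 and t5 as dependent variables. Neither names a baseline covariate.

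Recruitment, screening and randomization: "Eligible and consenting students from the same school will be stratified by gender (boy or girl) and age". Gender and age are therefore design variables, but as demographics they fall under the same conditional rule.

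**The concern.** Baseline depressive symptoms are named explicitly among the variables whose entry depends on an observed difference between arms. The sample size treats their entry as certain. An analyst who follows the analysis section can end up with a model that the power statement does not describe.

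The rule is also a poor way to choose covariates. Under randomisation a baseline difference between arms arises by chance, and its size says nothing about how strongly the variable predicts the outcome. A covariate earns its place by its correlation with the outcome, and the plan itself puts that correlation at .80. The rule makes the primary model depend on the data, and without a stated criterion it leaves the decision to the analyst.

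At stake is the variance reduction on which the sample size rests. There is no slack to absorb its loss: the Sample size section adds nothing for dropout, and Strengths and limitations expects a high number of dropouts.

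**Working it through.** **Inputs**, all from the Sample size section: two-sided alpha 0.05, power 0.80, d = 0.33 (outcome SD set to 1), r = .80, ICC 0.05, mean cluster size m = 5, coefficient of variation of cluster size 0.30, 64 per arm.

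**1. The plan's own figure.**
- Before clustering: n = 2(1.96 + 0.8416)²(1 − r²)/d² = 144.1 × 0.36 = 51.9, so 52 per arm.
- Design effect: 1 + [(1 + 0.30²) × 5 − 1] × 0.05 = 1.2225, stated as 1.22.
- 52 × 1.22 = 63.4, so 64 per arm and 256 in total.

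The stated sample size reproduces, and it depends on the factor 1 − .80² = 0.36.

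**2. Power at 64 per arm, with and without the t0 score.** The effective sample size is 64/1.2225 = 52.35 per arm.

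| | SE of the difference | d/SE | Power, Φ(d/SE − 1.96) | Detectable d, 2.8016 × SE |
|---|---|---|---|---|
| t0 CDI-2 in the model | √(2 × 0.36/52.35) = 0.117 | 2.81 | 0.80 | 0.33 |
| t0 CDI-2 left out | √(2/52.35) = 0.195 | 1.69 | 0.39 | 0.55 |

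**3. Sample size needed without adjustment.** 144.1 × 1.2225 = 176.2, so 177 per arm. Rounding 144.1 up to 145 first gives 145 × 1.2225 = 177.3, so 178.

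**4. How often the score would be left out.** The article gives no criterion, so two kinds are shown, each as an assumption.
- *A 5% significance test.* In a simulation with four arms, 13 groups of five per arm and ICC 0.05 (4,000 runs), the baseline score entered in about 5% of trials when the test allowed for clustering and about 9% when it did not. Power was 0.78 with the score always in, 0.38 with it never in, and 0.41 under the conditional rule with the test that ignores clustering. A separate simulation of 2,500 trials gave entry in 5.3% and power 0.40 under the rule.
- *A judgement by size.* The SD of a chance baseline difference between two arms is √(2 × 1.2225/64) = 0.195 SD. With four arms, the largest pairwise difference exceeds 0.20 SD in about 74% of trials and 0.25 SD in about 58%. On such a criterion the score would enter more often than not.

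**5. Scope.** The correlation of .80 is for t0 to t1. The article gives none for t4 or t5, so the power with adjustment at those times is not known. For illustration, at 64 per arm and d = 0.33 it would be 0.50, 0.56 or 0.66 at r = 0.5, 0.6 or 0.7. The unadjusted 0.39 does not depend on r.

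**The case against.** The strongest reply is that the Sample size section already says the primary outcome is evaluated in a baseline-adjusted ANCOVA. The analysis section says that variables which differ are entered; it does not say that the others are left out. Read together, the t0 score could always be in the model and the rule could only add extra covariates. A journal article may also leave the full covariate list to another document.

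The intent to adjust is indeed in the text, and that part stands. The reconciliation does not. If baseline depressive symptoms were always in the model, comparing them between arms to decide on covariates would have no purpose, yet they are the first variable named for that comparison. Nor is this something left to a later document: the article states a rule, and the rule conflicts with its own power basis.

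The reply is right against three stronger claims that a reader might infer.
- *That the adjusted analysis would usually not be run, with power near 0.40 in practice.* This needs a 5% test, which the article does not state. On a criterion by size the score could enter in more than half of trials.
- *That gender and age would be left out together with the baseline score in 95% of trials.* Each variable would be assessed separately, so a frequency for one does not carry over to the set.
- *That chance imbalance is a further harm.* A typical difference of about 0.20 SD at baseline carries about 0.16 SD (0.80 × 0.195) into the outcome, but this is the same variance already counted in the loss of power. The unadjusted comparison remains unbiased under randomisation.

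Finally, the fixed school effects may recover some precision. The article gives no figure for this, so 0.39 ignores any such gain.

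**Conclusion.** The concern holds as a conflict between two sections of the article. The sample size needs the t0 CDI-2 score in the model; the analysis section makes its entry depend on an unspecified difference between arms. Whenever the score is not entered, power at d = 0.33 falls from 0.80 to about 0.39, the detectable difference rises from 0.33 to about 0.55, and 177 to 178 per arm would be needed instead of 64. These figures take the plan's r, ICC and cluster sizes as given and no precision from the school effects.

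The article does not support a statement of how often this would happen. Under an assumed 5% test the score enters in about 5 to 9% of trials and power under the rule is about 0.40. Under an assumed judgement by size it could enter in most trials. In either case the primary model would be settled by chance imbalance.

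**What to change.** In Data analysis, delete the sentence that enters covariates according to observed differences. State instead that every model of CDI-2 depressive symptoms (t1, t4 and t5) includes the t0 CDI-2 score and the stratification variables gender and age, whatever the observed imbalance. Report baseline comparisons between conditions descriptively.

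As an optional extension, include the t0 CDI-2 score in the logistic models of the cost-effectiveness section. Those models carry no stated power, so this is not needed to resolve the conflict.

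The cost is one paragraph of wording. All the variables are already collected, and the sample size stays at 256.
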